### Hypotheses

The goal of this study is to integrate examination of affective, cognitive, and physiological risk factors for short-term changes in suicidal thinking and suicidal behaviors among adults known to be at high risk within an ideation-to-action framework. To that end, our hypotheses are as follows:

Hypothesis 1a (H1a): within-person increases in affective suicide risk factors conceptually related to psychache (negative affective experiences) will individually precede within-person increases in SI.Hypothesis 1b (H1b): negative affective experiences will co-occur in daily life such that they are best conceptualized as indices of a single latent construct capturing emotional distress (psychache), which will itself predict short-term increases in SI.Hypothesis 2a (H2a): among those with SI, higher baseline self-reported emotion-related impulsivity will predict greater odds of SA over follow-up.Hypothesis 2b (H2b): among those with SI, poorer baseline behavioral indices of inhibitory control in the context of negative affective stimuli will predict greater odds of SA over follow-up. We also predict that, among those with current SI during EMA, lower EMA-assessed inhibitory control will prospectively predict subsequent SA.Hypothesis 3a (H3a): during the EMA protocol, short sleep duration will predict within-person increases in SI.Hypothesis 3b (H3b): during the EMA protocol, short sleep duration will predict greater risk of next-day SA among those with SI.Exploratory hypothesis 3c (H3c): the within-person effects of short sleep duration on SA will be mediated by within-person changes in inhibitory control assessed during EMA.

A visual depiction of these hypotheses is provided in Figure 1.

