## Methods

### Project Overview

This is a single-group, repeated-measures (within-persons) observational study following adults with recent STB receiving inpatient psychiatric treatment (N=130). An ethnically diverse sample of participants will be recruited during inpatient psychiatric treatment in Lubbock, Texas, United States, based on past week STB. Eligible and interested participants will then complete the informed consent process, self-report surveys, clinical interviews, a computer task assessing cognitive inhibition, and a debriefing procedure. After discharge from inpatient care, participants will engage in a 4-week (28-day) EMA protocol that involves receipt of 7 signal-contingent self-report survey prompts per day between participants’ self-reported wake times and bedtimes. Participants will also be prompted to complete an abbreviated version of the cognitive inhibitory control task after each survey and asked to wear an actigraphy device for the 28-day follow-up period to assess objective indicators of sleep. Participants will be invited to complete a remote (phone or videoconference) follow-up interview assessing recent STB at 4 weeks and 8 weeks after discharge.

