### Power Analyses and Sample Size Considerations

Given variability in EMA adherence, we conducted power analyses for 100 participants, while planning to recruit 130 participants to account for those with inadequate compliance. Most study aims will be tested using dynamic structural equation modeling, as described herein. In a recent Monte Carlo simulation study [90], adequate power (>0.80) for modeling of a single process (eg, SI) was demonstrated for moderate effects where n=100 with as few as 50 repeated measures (*t*=50). Thus, this study (*t*=196, 7 prompts per day for 28 days) is well powered even with a compliance rate as low as 57.1% (112/196; 4 prompts per day for 28 days) to examine within-person processes (H1a, H1b, and H2b). To provide more conservative estimates of power, a series of simulations with 100 replications were conducted for a random-effects (multilevel) logistic outcome using R software (The R Foundation for Statistical Computing) [91]. The assumptions for these simulations were as follows: (1) n=100, (2) within-person effects for all predictors, (3) standard normal distributions for all predictors, and (4) an intercept variance of 0.3. On the basis of these models, the study is well powered (>0.8) to detect standardized within-person effects as low as 0.1 with compliance as low as 64%.

For H2a, we used G*Power (Heinrich Heine University) [92] to conservatively determine the minimum detectable effect predicting any SA over follow-up with n=100, Cronbach α=.05, and β=.8, controlling for a moderate effect of SI on SA (0.3). We assumed an event proportion of 10% for the outcome based on recent literature [93]. On this basis, the study is powered to detect an odds ratio >2.63 for the effect of baseline emotion-related impulsivity or inhibitory control on follow-up SA risk. By way of comparison, recent research has demonstrated significant predictors of follow-up SA risk with odds ratios from 6 [94] to 13 [93].

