#### Follow-up Interviews

Participants will be asked to complete a brief remote (phone or videoconference) follow-up interview assessing STB at 4 weeks and 8 weeks after discharge, with the goal of ensuring that the follow-up data capture all experienced STBs even if not reported on the EMA surveys. Specific follow-up interview items are provided alongside the Open Science Framework preregistration [89].

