For H2a, we will estimate the effects of baseline emotion-related impulsivity and inhibitory control on odds of SA over follow-up, controlling for between-person differences in SI severity. To do this, person-mean estimates of SI and person-maximum estimates of SA (yes or no) will be calculated using EMA data. SA can then be predicted by baseline emotion-related impulsivity and inhibitory control scores using logistic regression analysis, controlling for participants’ SI severity. For H2b, we will then test whether within-person changes in state inhibitory control precede subsequent SA among individuals reporting SI. Using a 2-level random slope model, we will model time *t* inhibitory control (controlling for inhibitory control measured at time *t–*1) as a predictor of time *t*+1 SA, controlling for time *t* SI.

For sleep-related hypotheses, we will use 2-level random slope models, as described previously, but in which survey-level data on SI and SA have been pooled to create day-level variables (because sleep varies at the daily, but not survey, level). For H3a, we will use person-mean–centered total sleep time on day *d–*1 to predict next-day (day *d*) SI, controlling for day *d–*1 SI. Models for H3b will parallel those used to test H2a, whereby total sleep time on day *d*-1 will be used to predict next-day SA (day *d*), controlling for day *d* SI. For H3c, we will test whether the sleep-SA association (H3b) is mediated by within-person changes in inhibitory control. Building on the H3b model, we will add in the effect of sleep on day *d–*1 predicting inhibitory control on day *d*. To ensure that we are capturing sleep-related changes in inhibitory control, inhibitory control on day *d* will also be regressed on inhibitory control measured on day *d–*1. Finally, day *d* inhibitory control will be used to predict day *d* SA, controlling for day *d* SI. Indirect and direct effects will be calculated and tested for significance using the MPlus *model indirect* command.

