### Methodological and Other Considerations

The primary methodological decisions in study design were with respect to the inclusion criteria, intensity of follow-up data collection methods, and level of monitoring and responsivity to indicators of suicide risk during follow-up.

First, we considered whether to limit the sample further (eg, individuals with recent SA) or whether to expand the inclusion criteria to include anyone receiving inpatient psychiatric care, regardless of recent STB. Individuals with a history of SA are at higher risk of later suicidal behavior than individuals with SI only [102], which would increase the odds of suicidal behavior during the follow-up period and plausibly increase statistical power. However, we felt that further restriction of the inclusion criteria would be likely to slow the speed of recruitment, a significant concern for a grant-funded study with a 2-year timeline. Recruiting a more heterogeneous sample will also allow us to examine the generalizability of predictors across a more diverse patient population. By contrast, expanding eligibility to all individuals receiving inpatient psychiatric care would likely reduce the odds of suicidal behavior over follow-up compared with individuals with recent STB [4].

Second, we considered the significant trade-offs between level of detail and frequency of follow-up assessments with the need to reduce participant burden (and, relatedly, the odds of attrition from the study). Prior research has shown that a greater number of surveys per day [103] and a greater number of items per survey [104] predict lower compliance with momentary assessment (EMA) research, which then affects the ability to adequately capture outcomes of interest (STB) during the EMA period. In addition, asking follow-up questions about the nuances of STB based upon *yes* responses during the EMA may increase the odds of participants choosing to deny these experiences that do occur to avoid additional follow-up questions, which take time and may be sensitive in nature. The duration and frequency of assessments chosen for this study were based on prior research suggesting that these parameters were feasible for the population of interest [105]. Finally, the 4- and 8-week follow-up interviews were added to the study protocol in response to grant reviewer feedback as a check against missed STB that were not captured during the EMA to increase statistical power for between-person models.

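### The H2a attempt outcome is built from EMA data alone, although the 4- and 8-week interviews were added to catch attempts that EMA misses and to raise power for between-person models.

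*Protocol article*

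**What the plan says.** The Hypotheses section words H2a as "higher baseline self-reported emotion-related impulsivity will predict greater odds of SA over follow-up", among those with suicidal ideation (SI), and gives no window. The Data Analysis Plan then fixes the variables: "person-mean estimates of SI and person-maximum estimates of SA (yes or no) will be calculated using EMA data". The model follows: "SA can then be predicted by baseline emotion-related impulsivity and inhibitory control scores using logistic regression analysis, controlling for participants’ SI severity". The baseline inhibitory-control part of H2b is therefore tested in the same regression.

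On timing, the Project Overview says "participants will engage in a 4-week (28-day) EMA protocol", and separately describes a "follow-up interview assessing recent STB at 4 weeks and 8 weeks after discharge".

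Two sections explain why the interviews exist. Follow-up Interviews says they should make the follow-up data "capture all experienced STBs even if not reported on the EMA surveys". Methodological and Other Considerations says they were added after grant review "as a check against missed STB that were not captured during the EMA to increase statistical power for between-person models".

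The power section assumes n=100 and 10% with an attempt, and concludes that "the study is powered to detect an odds ratio >2.63 for the effect of baseline emotion-related impulsivity or inhibitory control".

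**The concern.** The outcome definition and the stated purpose of the interviews do not fit together. The protocol gives a power reason for the interviews that can apply only to a between-person model of attempts, and then builds that model's outcome from a source that leaves them out. This is not a detail deferred to a fuller plan, because the article names the data source.

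Three kinds of attempt would be recorded at interview and still be coded as none in H2a:

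- an attempt within the 28 days that the participant did not report in EMA;
- an attempt within the 28 days after which the participant completed no further survey;
- an attempt in weeks 5 to 8.

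At n=100 and 10%, the model has about 10 attempters for three predictors (impulsivity, inhibitory control, SI severity), so losing even a few changes what it can detect. Leaving the source unsettled also leaves room to choose between EMA-only and combined counts after the attempts are known. With so few events, that choice could decide the result.

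**Working it through.** **Reproducing the stated figure.** Inputs from the power section: n = 100, event proportion p = 0.10, alpha 0.05, power 0.80 (printed as β), and an SI effect of 0.3. The Data Analysis Plan makes the H2a test two-tailed. I read 0.3 as a correlation between the predictor and SI, so R² = 0.09. For a standard-normal predictor the usual closed form is

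OR = exp[(z₀.₉₇₅ + z₀.₈₀) / √(n p (1−p)(1−R²))]

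- n p (1−p)(1−R²) = 100 × 0.10 × 0.90 × 0.91 = 8.19, with square root 2.862.
- OR = exp(2.802 / 2.862) = 2.66, against the stated 2.63.
- Power at 2.63 = Φ(0.967 × 2.862 − 1.960) = Φ(0.807) = 79%.

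The stated figure reproduces approximately. It would not if 0.3 were meant as R²: the two-sided result is then 3.05.

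**Dependence on who is counted.** The documents give neither the share of attempters that EMA captures nor the window behind the 10%. The capture shares and raised proportions below are therefore my assumptions. The formula is the same, with n = 100 and R² = 0.09.

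Case A: the 10% is complete ascertainment, and EMA captures only part of it.

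| EMA captures | Event proportion | Detectable OR | Power at 2.63 |
|---|---|---|---|
| 100% | 10% | 2.66 | 79% |
| 80% | 8% | 2.95 | 71% |
| 60% | 6% | 3.44 | 59% |
| 50% | 5% | 3.85 | 52% |

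For the last row: 100 × 0.05 × 0.95 × 0.91 = 4.32, square root 2.079; exp(2.802 / 2.079) = 3.85; Φ(0.967 × 2.079 − 1.960) = Φ(0.05) = 52%.

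Case B: the 10% is already the EMA-only proportion, and the interviews add to it.

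| With interviews | Detectable OR | Power at 2.63 |
|---|---|---|
| 12% | 2.47 | 85% |
| 15% | 2.28 | 91% |

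In case A the EMA-only outcome falls short of the planned power. In case B it forgoes power that the interviews would supply.

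**Separate check on the 2.63.** The closed form is a large-sample approximation. Simulating the three-predictor logistic model at n = 100, 10% events, OR 2.63 and SI log-odds ratio 0.3 gives:

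- about 64–66% (Wald) and 68–71% (likelihood ratio) when the predictors are correlated at 0.3;
- about 73–74% (Wald) and 77% (likelihood ratio) when they are uncorrelated.

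The correlations are assumed. This shortfall arises whichever source defines the attempt, so it bears on the 2.63 and not on the EMA-only choice.

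**The case against.** Several points on the other side stand.

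- A reader might infer that every attempt during a missed prompt is lost. It is not. Table 2 shows that the suicidal-behavior item asks about the time since the last survey, so the next completed survey can pick it up. Staff also contact participants after days of non-response. Within the 28 days, the loss is confined to unreported attempts and to those with no later completed survey.
- A reader might infer that weeks 5 to 8 certainly belong to H2a. The article also uses the term follow-up for the 28-day period, and neither the hypothesis nor the power section gives a window. The window is ambiguous.
- A reader might infer that the interviews are deliberately excluded. The plan names EMA and excludes nothing expressly, and the power rationale speaks of between-person models without naming H2a. No other between-person attempt model is planned, however, and no analysis uses the interviews.
- A reader might infer that power is only 36%. That needs the 10% to be an 8-week risk, a constant hazard that puts half the events after day 28, correlated predictors and a Wald test. The documents do not establish these.
- A reader might infer that the odds ratio is biased because impulsive participants comply less. No section supports that link. If capture does not vary with the predictors and there are no false positives, an outcome this rare gives only slight attenuation, and the main cost is lost events.

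None of this reconciles the EMA-only definition with the stated purpose of the interviews.

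**Conclusion.** The inconsistency is textual and holds without any power figure: the only between-person attempt model takes its outcome from EMA, while the interviews added to support such models have no role in the analysis. Followed as written, the plan codes attempts disclosed only at interview as non-events. This misclassifies the outcome and loses scarce events.

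The documents do not fix the size of the loss. The fall from about 79% to 52–71% assumes that the 10% means complete ascertainment, that EMA captures 50–80% of those participants, that n = 100 and that R² = 0.09.

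It would go too far to say that the stated 80% power is simply wrong. The 2.63 reproduces closely in closed form, and simulation at 10% events gives roughly 64–77%, so it is somewhat optimistic. An analysed sample nearer the 130 to be recruited would narrow that gap.

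**What to change.** Settle the outcome before the attempt data are analysed:

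1. Define the H2a outcome, and with it the baseline part of H2b, as any suicide attempt reported in EMA or at the 4- or 8-week interview.
2. State the window (4 or 8 weeks after discharge), and use the same one in the hypothesis, the model and the power section.
3. State how a missing interview is handled, and how participants without EMA SI data are handled. The SI covariate is an EMA person-mean, so someone with interview data only has no value for it.
4. Keep the EMA-only attempt outcome as a sensitivity analysis.
5. Say which window and ascertainment the 10% refers to, and restate the detectable odds ratio for the combined outcome, preferably by simulating the three-predictor model.

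The cost is a few sentences and one sensitivity analysis. The interviews are already in the protocol and compensated. The Results section still anticipates completion of data collection, so there is time to make the change. There are two drawbacks: some attempts will rest on interview recall, and with an 8-week window, SI measured in weeks 1 to 4 would adjust for attempts up to week 8.

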#### Data Analysis Plan

Before conducting analyses, we will clean and check data for errors, address outliers, ensure that statistical assumptions for analyses have been met, and examine potential confounders to include in subsequent analyses as warranted. Variables that may exhibit skewness (eg, number of lifetime episodes of NSSI) will be examined for skewness and kurtosis and, if necessary, either rank transformed or log transformed. We will include the effect of time (196 prompts over 28 days) to account for habituation and examine potential nonlinear effects of, for instance, age. Most analyses will use time-series (dynamic) structural equation modeling [98,99], which uses Bayesian estimation, conducted with MPlus statistical software (Muthén & Muthén) [99]. Dynamic structural equation modeling is robust with regard to high rates of missing data, zero-inflated categorical variables, and variable time intervals among observations, all of which are common in EMA with these types of data, and allows for latent decomposition of constructs into their constituent between- and within-person components [98]. Dynamic structural equation modeling also facilitates within-person lagged analyses to examine prospective relationships between time *t* predictors and time *t*+1 outcomes; by controlling for autoregressive effects over time, these methods can model within-person change in constructs over time.

For H1a, we will examine whether within-person changes in negative affective experiences precede proximal within-person changes in SI using 2-level random slope models. Each of 7 momentary negative affective experiences reported at time *t* will be regressed on itself at time *t–*1, producing a measure of residualized change in each negative affective experience. Momentary SI reported at time *t* will be regressed on itself at time *t–*1, as well as the 7 negative affective experience change indicators, yielding an estimate of the within-person effect of changes in all negative affective experiences on subsequent within-person changes in SI, controlling for autoregression. For H1b, we will examine the within- and between-person factor structures of the 7 negative affective experiences using multilevel exploratory factor analysis [100]. Using established best practices, we will identify the most appropriate structure and use these within-person factors to predict changes in SI over time, similar to the procedures used for H1a.

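### H2a fits two or three slopes to about 10 attempters; ordinary maximum-likelihood logistic regression would overstate non-null odds ratios, and Firth penalization largely corrects this at a small price

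*Protocol article*

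**What the plan says.** In the Data Analysis Plan of the protocol article, H2a reduces the EMA data to a person-mean for SI and a yes/no indicator of any SA per person. Then "SA can then be predicted by baseline emotion-related impulsivity and inhibitory control scores using logistic regression analysis", "controlling for participants’ SI severity". The later paragraph on inference sets H2a apart from the Bayesian models and judges it by two-tailed P<.05. The opening paragraph of the plan also lets the team "examine potential confounders to include in subsequent analyses as warranted".

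Under Power Analyses and Sample Size Considerations, the H2a calculation is made "with n=100, Cronbach α=.05, and β=.8" (evidently significance level .05 and power .80). On the outcome: "We assumed an event proportion of 10% for the outcome based on recent literature". It concludes that "the study is powered to detect an odds ratio >2.63" for baseline impulsivity or inhibitory control. The analysed 100 come from "planning to recruit 130 participants to account for those with inadequate compliance".

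The article does not name an estimator for H2a. It mentions no penalization, no handling of separation and no limit on added covariates.

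**The concern.** Maximum-likelihood log odds ratios have a finite-sample bias away from zero, which grows as events per coefficient fall. The article's own figures give about 10 events. If impulsivity, inhibitory control and SI severity share one model, that is 3.3 events per slope, and any added confounder lowers it further. In that range a real association will on average be reported as larger than it is. If attempts turn out rarer than assumed, some data sets will separate and have no finite estimate. What is at stake is how large the person-level associations with attempt appear to be, in a study meant to inform intervention targets.

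**Working it through.** **1. Inputs from the article.** n=100 analysed, 130 recruited, event proportion 10%, two-sided .05, power .80, covariate adjustment 0.3, minimum detectable odds ratio 2.63.

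**2. The article's own figure.** For a standard-normal predictor, the usual formula is n = (z₀.₉₇₅ + z₀.₈₀)² / [p(1−p) b² (1−R²)], with b the log odds ratio. Reading 0.3 as a correlation, R² = 0.09. Then b² = 7.849 / (100 × 0.09 × 0.91) = 0.958, b = 0.979 and OR = 2.66. At OR 2.63 (b = 0.967) the formula needs n = 102.5 and gives power 0.790 at n=100. The stated 2.63 is therefore reproduced closely.

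**3. Events per slope.**
- 100 × 0.10 = 10 events: 10/3 = 3.3 per slope with three predictors, 10/2 = 5 with two.
- If all 130 were analysed: 13 events, 13/3 = 4.3 with three predictors and 13/2 = 6.5 with two.

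**4. Simulation.** Three standard-normal predictors, SI odds ratio 1.7 per SD, 3,000 replicates per scenario. The true log OR at 2.63 is 0.967, and bias is the mean divided by 0.967, minus 1. The SI odds ratio, the correlations and the predictor distributions are assumptions, not figures from the article. A separated sample has no finite maximum-likelihood (ML) estimate, so the ML means can only describe the others.

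| n | Events | True ORs (two target predictors) | Correlation | ML mean log OR (bias) | Firth mean log OR (bias) | RMSE, ML → Firth |
|---|---|---|---|---|---|---|
| 100 | 10 | 2.63, 2.63 | 0 | 1.124 (+16%) | 0.972 (+1%) | 0.602 → 0.466 |
| 100 | 10 | 2.63, 2.63 | 0.3 | 1.176 (+22%) | 0.990 (+2%) | 0.750 → 0.542 |
| 100 | 10 | 2.63, 1.00 | 0.3 | 1.112 (+15%) | 0.973 (+1%) | 0.592 → 0.475 |
| 130 | 13 | 2.63, 2.63 | 0.3 | 1.086 (+12%) | 0.969 (0%) | 0.543 → 0.474 |
| 100 | 20 | 2.63, 2.63 | 0.3 | 1.064 (+10%) | 0.961 (−1%) | 0.452 → 0.386 |
| 100 | 5 | 2.63, 2.63 | 0.3 | 1.234 (+28%) | 0.972 (+1%) | 0.989 → 0.716 |
| 100 | 10 | 1.00, 1.00 | 0.3 | 0.005 (none) | 0.004 (none) | 0.443 → 0.393 |

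Repeat runs of the three-predictor models at 10 events gave 14-19%. With two predictors (one target plus SI) the ML bias was 7-14%, and about 9% at n=130. Together these give roughly 10-20% at n=100 and 7-12% at n=130. In the repeat runs Firth stayed within about 2% at 10 or more events and within 3% at 5% events.

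**5. Separation.** At 10 events and OR 2.63, 0.1-0.3% of samples separated or failed to converge. At 5 events it was about 4-6%.

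**6. Tests.** With no effect, rejection at .05 was 0.050 for ML Wald, 0.063 for the ML likelihood-ratio (LR) test and 0.049 for Firth's penalized LR test (10 events, correlation 0.3). With both odds ratios 2.63 and correlation 0.3, power was 0.573, 0.642 and 0.594 in the same order.

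**7. Predicted risk.** Firth's mean predicted risk was 0.110 against 0.101 observed at 10 events, and 0.064 against 0.052 at 5 events.

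**The case against.** **The estimator is not stated.** Firth regression is itself logistic regression, and a small-sample correction could sit in the fuller plan. This stands as a caveat. But the article does fix a method and a decision rule for H2a, and logistic regression without qualification ordinarily means maximum likelihood.

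**Three predictors in one model is only one reading.** The Hypotheses section puts baseline impulsivity under H2a and baseline inhibitory control under H2b, and the power section treats them as alternatives. This stands, and it is why the two-predictor range is included. A reader might infer that H2a should move to separate models to gain events per slope. The bias does not justify that, because it would change joint effects into separate ones.

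**Sampling error dominates.** The ML bias is about 0.15-0.21 log units in the three-predictor scenarios at 10 events, against an RMSE of 0.59-0.75. Medians tell a milder story: across the runs the median ML odds ratio was 2.82-2.96 and the median Firth one 2.48-2.56, against 2.63. Estimates selected for significance stay inflated under Firth too (mean OR 3.4-3.5, against 4.0-4.4 under ML). All of this is right. Firth reduces mean bias and RMSE; it does not add information.

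**False positives.** A reader might infer that the P<.05 rule is unsafe. It is not under the Wald test, whose size was 0.04 to 0.05. The ML LR test was mildly liberal, at 0.063.

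**Benchmarking.** A reader might infer that inflated H2a estimates will be set against the published odds ratios of 6 to 13. The power section compares those only with the minimum detectable 2.63 and plans no such comparison of results.

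**Conclusion.** The point holds as a recommended improvement. With the article's own n and event proportion, ordinary maximum likelihood would overstate a non-null H2a odds ratio: the mean log odds ratio is roughly 10-20% too high at the target of 2.63, and about 7-12% if all 130 are analysed. At about 5 events, a few percent of fits separate.

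The size rests on standard-normal predictors, an SI odds ratio of 1.7, correlations of 0 to 0.3, and the assumed 10% event proportion. The upward direction appeared in every non-null scenario tried, and there is no bias at an odds ratio of 1.

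A reader might infer that Firth's method costs nothing. It does have a price: penalized LR power was 1 to 5 points below the ML LR test, part of which reflects that test's inflated size. It was equal to or slightly above Wald. Unmodified Firth also pulls predicted risks upward at these event rates. These costs are small beside the gain in bias and RMSE, but they should be acknowledged.

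**What to change.** In the H2a paragraph of the Data Analysis Plan, name Firth penalized-likelihood logistic regression as the estimator. Use the penalized likelihood-ratio P value (two-sided .05 unchanged) and profile penalized-likelihood 95% confidence intervals. Keep the planned predictors and the SI adjustment. Because each extra covariate lowers events per slope, also say how many confounders may enter this model.

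The change is one or two sentences, uses standard software and needs no new data. Reported odds ratios will be somewhat less extreme. If predicted risks are reported, state that an intercept correction will be applied.
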